## Abstract

**Background:**

Post-stroke cognitive impairment (PSCI) is a common stroke complication, significantly reducing patients’ quality of life and increasing caregiving burden. Repetitive transcranial magnetic stimulation (rTMS) of the left dorsolateral prefrontal cortex (L-DLPFC) improves cognition but with limited efficacy. Stimulation of Neiguan (PC6), a key acupoint in traditional Chinese medicine, modulates cognition-related brain networks.

**Objective:**

To compare cognitive improvement and brain network remodeling in PSCI patients who receive rTMS over the L-DLPFC combined with (1) PC6 magnetic stimulation (MAG), (2) PC6 acupuncture (ACU), or (3) PC6 sham magnetic stimulation (SHM).

**Methods:**

This three-arm randomized controlled trial will enroll 105 patients with PSCI, randomly allocated 1:1:1 to the MAG (*n* = 35), ACU (*n* = 35), and SHM (*n* = 35) groups. Interventions will be administered 5 times/week for 3 weeks. All groups will receive high-frequency rTMS over the L-DLPFC (10 Hz, 80% rest motor threshold). The primary outcome is the Montreal Cognitive Assessment (MoCA) change from baseline to week 3. Secondary outcomes include the Mini-Mental State Examination (MMSE), Modified Barthel Index (MBI), Hamilton Anxiety Rating Scale (HAMA), Hamilton Depression Rating Scale (HAMD), Pittsburgh Sleep Quality Index (PSQI), and adverse events. Functional magnetic resonance imaging (fMRI) and functional near-infrared spectroscopy (fNIRS) data will be acquired at baseline and post 3-week treatment. Clinical data will be analyzed via SPSS 26.0 using repeated measures analysis of variance (ANOVA) to compare intergroup changes in outcomes across time points. Neuroimaging data will be processed in MATLAB R2018a. Correlation analyses will assess associations between clinical scores and neuroimaging parameters.

**Conclusion:**

This study will provide the first randomized controlled evidence for acupoint magnetic stimulation in PSCI, demonstrating that adding MAG to L-DLPFC rTMS confers additional cognitive benefits. Its mechanism in reshaping brain networks will be elucidated via fNIRS-fMRI, which is expected to accelerate clinical translation of non-pharmacological interventions.

**Clinical trial registration:**

https://www.chictr.org.cn/, identifier ChiCTR2400090768.

## Introduction

Post-stroke cognitive impairment (PSCI) is one of the common sequelae in stroke survivors (1). Globally, the incidence of PSCI varies due to regional differences and diagnostic criteria, with approximately one-third to one-half of stroke patients demonstrating cognitive impairment during follow-up (2). PSCI not only reduces patients’ ability to perform activities of daily living but also significantly increases disability and mortality rates, imposing a heavy burden on families and society (3). China is one of the countries bearing the greatest global burden of stroke, both in terms of incidence and disease impact (4). Currently, no pharmacological therapy has proved universally effective for PSCI, making non-pharmacological interventions a key focus of research (5).

Cognitive deficits following stroke are linked to large-scale network dysfunctions, including disrupted frontotemporal connectivity within and between the default-mode networks (DMN), salience networks (SN), and central executive networks (CEN) (6–9). High-frequency repetitive transcranial magnetic stimulation (rTMS) targeting the left dorsolateral prefrontal cortex (L-DLPFC) may be the most promising approach for improving overall cognitive function after stroke, with no significant safety concerns (10). Targeted stimulation of the DLPFC, an essential hub for working memory, attention, and executive control, may enhance cortical excitability and thereby underlie its therapeutic benefit (11). Building on central stimulation, repetitive peripheral magnetic stimulation (rPMS) delivers high-intensity magnetic pulses to peripheral nerves, inducing proprioceptive afference that up-regulates sensorimotor cortices and mitigates motor-cognitive deficits (12, 13).

In addition to magnetic neuromodulation, acupuncture as a cornerstone of traditional Chinese medicine (TCM) has been widely used in cognitive rehabilitation. Endorsed by the World Health Organization (WHO) in 2002 as an adjunctive therapy for vascular dementia (14), acupuncture therapy (manual, electro-, and moxibustion) have repeatedly improved cognitive outcomes (15). Among acupoints, Neiguan (PC6) is a primary target for cognitive disorders (16). Functional magnetic resonance imaging (fMRI) reveals that PC6 stimulation modulates vestibulo-autonomic regions (cerebellar flocculonodular lobe, hypothalamus, insula) and key cognitive networks such as the default-mode and anterior cingulate cortices (17, 18). In recent years, research teams have attempted to apply modern magnetic stimulation techniques to traditional acupoints. Recent studies have applied magnetic stimulation to PC6, reporting enhanced small-world properties and interregional synchrony within cognitive networks, thereby facilitating information transfer (19, 20). These findings imply a dual mechanism: classical meridian regulation combined with direct neuromodulation, potentially yielding adjunctive cognitive benefits.

Advances in neuroimaging enable multidimensional tracking of post-stroke brain reorganization. Functional near-infrared spectroscopy (fNIRS) and fMRI are the principal tools. fNIRS provides portable, bedside-capable monitoring of cortical hemodynamics (21), with studies revealing reduced inter-hemispheric connectivity in PSCI patients compared to controls (22). Resting-state fMRI, by mapping spontaneous BOLD synchrony, excels at delineating whole-brain functional network integrity and its disruption in PSCI (23, 24). Integrating fNIRS, fMRI, and other modalities merges functional and structural data, offering a comprehensive view of network states and an objective means of evaluating intervention efficacy.

This prospective randomized controlled trial (RCT) will assess whether magnetic stimulation at PC6 improves cognition in PSCI and clarifies its neural basis. We hypothesize that, compared to the control intervention, the PC6 magnetic stimulation will significantly improve patients’ overall cognitive level and exhibit specific neuroplastic changes in brain functional networks. As the first multimodal study integrating acupoint therapy with neuromodulation, this research will provide new insights and high-quality evidence for non-pharmacological management of PSCI.

## Method and analysis

### Research design

The present study is a three-arm RCT. Eligible PSCI patients will be enrolled from the Inpatient Department and Outpatient Clinic of Rehabilitation Medicine, West China Hospital, Sichuan University. Participants will be randomized in a 1:1:1 ratio to three groups: PC6 Magnetic Stimulation (MAG), PC6 Acupuncture (ACU), and Sham Magnetic Stimulation at PC6 (SHM). All three groups will concurrently receive rTMS (targeting the L-DLPFC). The study flowchart is presented in Figure 1, and assessment time points are detailed in Table 1. Ethical approval was granted by the Ethics Committee of West China Hospital of Sichuan University on March 13, 2024 (Approval No.: 20240313). The trial is registered at the Chinese Clinical Trial Registry: https://www.chictr.org.cn/, Registration No.: ChiCTR2400090768.

**Figure 1 fig1:**
[figure not shown]
Trial flow chart. MoCA, Montreal Cognitive Assessment; MMSE, Mini-Mental State Examination; MBI, Modified Barthel Index; HAMD, Hamilton Depression Rating Scale; HAMA, Hamilton Anxiety Rating Scale; PSQI, Pittsburgh Sleep Quality Index.

**Table 1 tab1:** Details of the planned visit schedule.

Stage	Baseline period	Treatment period			Follow-up period	
TimePoint	0	Week 1	Week 2	Week 3	Week 8	Week 12
Enrollment						
Eligibility screen	×					
Informed consent	×					
Demographic characteristics	×					
Medical history	×					
fNIRS	×			×		
fMRI	×			×		
Interventions						
Magnetic Stimulation Group		×	×	×		
Acupuncture Group		×	×	×		
Sham Magnetic Stimulation Group		×	×	×		
Assessments						
MoCA	×			×	×	×
MMSE	×			×	×	×
MBI	×			×		
HAMA	×			×		
HAMD	×			×		
PSQI	×			×		
Patient safety						
Adverse events		×	×	×		

### Diagnostic criteria

Refer to the diagnostic criteria for PSCI in the Scientific Statement on Cognitive Impairment After Ischemic and Hemorrhagic Stroke (25), published by the American Heart Association/American Stroke Association (AHA/ASA) in 2023.

### Inclusion criteria

Aged 30–75 years, right-handed;Definite history of stroke, with clinical and imaging evidence supporting the diagnosis;Presence of impairment in one or more cognitive domains, with a MoCA score <26;Stable vital signs;Written informed consent from the patient or legal guardian.

### Exclusion criteria

Unstable vital signs or uncontrolled severe respiratory/circulatory complications;Recurrent stroke or multiple lesion strokes;Pre-existing epilepsy, cognitive impairment, depression, other psychiatric disorders;Secondary cognitive impairment (e.g., excessive alcohol consumption);Severe dysfunction of other organs or critical systemic diseases;Severe visual/hearing impairments or aphasia precluding cooperation;Neurodegenerative cognitive disorders (e.g., frontotemporal dementia);Contraindications for rTMS treatment and MRI examination: Metallic implants/electronic devices, skull defects, etc.

### Withdrawal criteria

A participant will be withdrawn from the trial if any of the following conditions occur:Serious adverse reactions requiring termination, as determined by a specialist physician;Worsening symptoms or severe complications necessitating emergency measures;Identification of critical safety concerns by investigators;Voluntary withdrawal for personal, family, or social reasons that precludes completion of the treatment course.

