### Statistical analysis

#### Clinical data analysis

All analyses will be performed using SPSS 26.0 (IBM, Armonk, NY, USA) with two-tailed tests (*p* < 0.05). Quantitative data will be expressed as mean ± standard deviation. Within-group comparisons will use paired t-tests. Between-group comparisons will employ one-way ANOVA or nonparametric rank-sum tests (Kruskal-Wallis test), depending on data distribution. Count data will be presented as numbers (percentages), to be analyzed by *χ*^2^ tests, Fisher’s exact tests, or Ridit analysis. Repeated-measures ANOVA with Greenhouse–Geisser correction will be applied to evaluate longitudinal changes across timepoints. Both intention-to-treat (ITT) and per-protocol (PP) analyses will be conducted. In the ITT analysis, missing outcome data will be handled using multiple imputation under the assumption of missing at random. For the primary outcome (MoCA), we will report effect sizes and 95% confidence intervals for between-group differences in score changes. Clinical relevance will be interpreted using published MoCA change ranges and distribution-based benchmarks, rather than a prespecified minimal clinically important difference (MCID). Pearson’s or Spearman’s correlation coefficients (selected based on data distribution) will be calculated to examine associations between clinical scales and neuroimaging parameters. Covariates including age, sex, years of education, time from stroke onset to study enrollment, and a quantitative metric capturing the “dose” of conventional rehabilitation (derived from documented type, frequency, and duration), and lesion side (left/right) will be incorporated into a multivariate linear regression model evaluating the primary endpoint (change in MoCA score) and key secondary cognitive outcomes. Furthermore, to explore the potential modifying effect of lesion side on treatment response, we will conduct an exploratory analysis by adding a Group × Lesion Side interaction term to the primary multivariate model for the MoCA change score and key imaging outcomes. These interaction analyses will be explicitly labeled as exploratory, and their results will be interpreted cautiously due to the limited statistical power for detecting interaction effects.

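### The withdrawal rule takes patients out of the trial, not only off treatment, so primary outcomes lost for clinical reasons would have to be imputed under missing at random

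*Protocol article*

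**What the plan says.** The Withdrawal criteria section of the protocol article opens with "A participant will be withdrawn from the trial if any of the following conditions occur". Four conditions follow. Two describe the patient's clinical course: "Serious adverse reactions requiring termination, as determined by a specialist physician" and "Worsening symptoms or severe complications necessitating emergency measures". A third is a critical safety concern identified by investigators. The fourth is "Voluntary withdrawal for personal, family, or social reasons that precludes completion of the treatment course".

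The abstract fixes the endpoint: "The primary outcome is the Montreal Cognitive Assessment (MoCA) change from baseline to week 3". Treatment lasts three weeks. Table 1 schedules MoCA and MMSE at baseline and at weeks 3, 8 and 12, with none at weeks 1 or 2.

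On analysis, the Clinical data analysis section states "Both intention-to-treat (ITT) and per-protocol (PP) analyses will be conducted" and adds "In the ITT analysis, missing outcome data will be handled using multiple imputation under the assumption of missing at random".

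**The concern.** Ending the study intervention and ending a patient's participation are different decisions, and the Withdrawal criteria section merges them. The listed conditions are reasons why treatment might stop, but the stated consequence is leaving the trial. The fourth condition shows the merging most clearly, because it ties leaving the trial to not finishing treatment. Nothing in the article says that a withdrawn patient is still assessed.

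Followed as written, the rule makes primary outcomes missing, in part for reasons linked to how the patient is doing. Imputation under missing at random would then give such a patient a week-3 MoCA predicted largely from patients who stayed in. If the withdrawn patients did worse than that prediction, their arm's mean change is too favourable. If the arms differ in how many such patients they lose, the treatment comparison is distorted in favour of the arm that loses more. An analysis plan can examine this by sensitivity analysis, but it cannot recover scores that were never collected.

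**Working it through.** **1. Which outcomes are lost.** The conditions apply at any time in the trial. A patient withdrawn after week 3 already has the primary outcome. A patient withdrawn during the three treatment weeks has a baseline MoCA and, because Table 1 has no MoCA at weeks 1 or 2, no later one. The imputation model therefore has no on-treatment cognitive score for exactly the patients whose primary outcome is missing. It can use baseline scores, the listed covariates and, if the analyst includes them, recorded adverse events.

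**2. The plan's own figures.** Inputs from the Sample size section: three groups, f = 0.32, alpha 0.05, power 0.80, 99 patients, 10% attrition, target 105.
- One-way ANOVA with noncentrality N × f² gives power 0.808 at N = 99, so the stated 99 is reproduced.
- Ten per cent of 105 is 10.5, so about 10 to 11 patients (3 to 4 per arm) would lack an observed outcome.
- That leaves 94 to 95 observed, at which the same calculation gives power of about 0.79.

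**3. Bias in a between-arm difference.** Let p be the proportion missing in an arm and δ the amount by which the missing patients' true mean change falls below what missing at random imputes. The imputed arm mean is too high by p × δ, so

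bias = p₁δ₁ − p₀δ₀, which is (p₁ − p₀) × δ when δ is the same in both arms.

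The document gives neither the split by arm nor δ. All values below are assumptions.

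| Missing, arm 1 vs arm 0 | δ | Bias |
|---|---|---|
| 10% vs 10% | any common value | 0 |
| 15% vs 5% | 2 points | 0.10 × 2 = 0.2 points |
| 15% vs 5% | 3 points | 0.10 × 3 = 0.3 points |
| 15% vs 5% | 0.5 to 1.5 SD | 0.05 to 0.15 SD |
| 20% vs 0% | 0.5 to 1.5 SD | 0.10 to 0.30 SD |

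For scale, if one arm differs from two equal arms, f = 0.32 corresponds to d = 3 × 0.32 / √2 = 0.68. The SD rows then run from 0.05/0.68, about 7%, to 0.30/0.68, about 44%, of that effect. The upper end needs every loss to fall on one side of the comparison and a 1.5 SD deficit.

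**4. Mixed reasons for leaving.** These rows apply δ to every missing patient. If, say, half the losses in each arm were for family or social reasons and fitted missing at random, the average δ halves, and 0.2 to 0.3 points becomes 0.10 to 0.15.

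**The case against.** The strongest reply is that loss of data after withdrawal is inferred. The Withdrawal criteria section does not say that assessments stop, the visit schedule does not exclude withdrawn patients, and an ITT analysis separate from per-protocol is planned. The full protocol behind the article may say what is collected afterwards. This is fair, and it limits the point to what the article states. But the stated consequence is leaving the trial, and nothing in the article keeps these patients in follow-up, so site staff who follow it would have no ground for calling them back.

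Several stronger readings are tempting and are not supported:
- **That missing at random assumes the reverse of what the rule does.** It does not. It allows missingness to depend on observed data and excludes only further dependence on unobserved values. The weakness here is the lack of any cognitive score between baseline and week 3.
- **That every patient who declines or misses sessions is withdrawn.** The worsening condition may well be limited to cases that need emergency measures, and the last condition covers voluntary withdrawal only.
- **That harm is hidden.** Adverse events are scheduled in weeks 1 to 3, must be documented, and are a listed secondary outcome. What may be lost is the effect of such events on MoCA.
- **That the comparison will be biased.** All arms receive active L-DLPFC rTMS and intensive rehabilitation, so many reasons for withdrawal should be shared. Treating physicians are unblinded, and the section does not say that those who decide on withdrawal are blinded, so unequal withdrawal is possible. Nothing in the document shows that it will occur.

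The lack of a named analysis departing from missing at random is also no fault in a protocol article, since the SAP may hold it.

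**Conclusion.** The point holds as a weakness in how the rule is written. As stated, it removes patients from the trial for clinically related reasons, and for those who leave during treatment the primary outcome must be imputed from baseline information only. Missing at random is least credible for serious reactions, emergency worsening and safety concerns; it may be adequate for personal or family reasons.

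The size cannot be fixed from the document. The bias is zero when withdrawal and the departure from missing at random are equal across arms. It is 0.2 to 0.3 MoCA points, in favour of the arm with more withdrawals, under an assumed 15% against 5% split and a 2 to 3 point deficit in all missing patients. It is smaller if some of them fit missing at random. On a 30-point scale that is modest, but the loss cannot be repaired after the fact and is cheap to prevent. Whether the clinical conditions themselves are right is not judged here.

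**What to change.** Leave the conditions for stopping treatment as they are and change their consequence. Reword the Withdrawal criteria section so that these events end the study intervention only. All randomised patients stay in the already scheduled MoCA and MMSE assessments at weeks 3, 8 and 12 unless they withdraw consent for data collection. Analyse them in the arm to which they were randomised, and impute only what is still missing. If the full protocol already says this, bring the article's wording into line with it. A sensitivity analysis that imputes worse outcomes than missing at random would be a useful addition, but it is optional and can sit in the SAP.

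The cost is a change of wording in the protocol and consent form, and some effort to bring back patients who have stopped treatment. Not all can be assessed: some will decline visits, and some may be too unwell for a MoCA at week 3. The gain is therefore at most about 10 of the 105 outcomes, which is the whole 10% attrition allowance, and probably fewer.

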### Sample size

This study employes a three-arm, parallel-group, randomized controlled design (1:1:1 allocation), with the MoCA score as the primary endpoint. One-way analysis of variance (ANOVA) is used to compare differences among the three groups. Due to the lack of a clear anticipated effect size, based on previous rTMS studies in PSCI (26–28), we adopt Cohen’s f ≈ 0.32 as the expected effect size. Using G*Power 3.1 (test type: one-way ANOVA; effect size *f* = 0.32; *α* = 0.05, two-tailed; power = 0.80), the estimated total sample size is 99 (33 per group) to detect significant differences in MoCA scores. To account for a potential 10% attrition rate, the final recruitment target is set at 105 participants (35 per group). Because *a priori* information on within-subject correlation and covariate R^2^ was unavailable, we used one-way ANOVA for conservative planning. The primary analysis will use longitudinal models with covariate adjustment, which is expected to provide equal or greater efficiency than the planning model.

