## Discussion

This protocol describes a three-arm randomized controlled trial designed to determine whether PC6 magnetic stimulation provides additional cognitive benefit when combined with standard left DLPFC rTMS in patients with post-stroke cognitive impairment, and to characterize associated network-level remodeling using combined fNIRS-fMRI. By comparing PC6 magnetic stimulation with PC6 acupuncture and sham magnetic stimulation at PC6 while holding left DLPFC rTMS constant across arms, the study aims to quantify the incremental effect of PC6 magnetic stimulation versus sham and to compare magnetic stimulation with acupuncture. The trial’s multimodal imaging framework is expected to provide mechanistic insight into how this combined “central regulation and peripheral input” strategy may reshape cognition-related networks.

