This study also incorporates numerous methodological considerations aimed at enhancing the quality of evidence and the reliability of result interpretation. First, we employed a three-arm randomized controlled design, where all participants received conventional high-frequency rTMS targeting the L-DLPFC, with additional PC6 intervention introduced as a variable. This design ensures ethical compliance while attributing intergroup differences to the specific effects of either magnetic stimulation or acupuncture at PC6. Since rTMS has been demonstrated to have therapeutic benefits for PSCI (56, 57), we avoided exposing the control group to entirely ineffective treatments, thereby safeguarding patient welfare. However, it is important to acknowledge that this approach may reduce the significance of intergroup differences. To address this, we ensured sufficient statistical power through rigorous sample size estimation and balanced enrollment criteria. Second, regarding blinding procedures, we implemented both assessor and patient blinding to the greatest extent possible. Although acupuncture and magnetic stimulation differ in somatosensory perception, the sham stimulation group used a simulated coil placed over PC6 without delivering pulses, making it difficult for participants to discern whether they received actual magnetic stimulation. All clinical assessments were conducted by independent evaluators unaware of group assignments to minimize subjective bias.

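### The stated 80% power belongs to a three-group omnibus test, not to MAG versus sham, and no planned analysis names MAG versus sham as the primary contrast

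*Protocol article*

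**What the plan says.** **The question.** The Introduction hypothesises that, "compared to the control intervention, the PC6 magnetic stimulation will significantly improve patients’ overall cognitive level". The Discussion says the study will "quantify the incremental effect of PC6 magnetic stimulation versus sham and to compare magnetic stimulation with acupuncture". The Abstract's objective lists all three arms without ranking the comparisons.

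**The sizing.** Under Sample size: "One-way analysis of variance (ANOVA) is used to compare differences among the three groups". The effect size is f of about 0.32, adopted "based on previous rTMS studies in PSCI" after the authors concede that they have no clear expected effect. With alpha 0.05 and power 0.80 the result is 99 patients (33 per group), raised to 105 (35 per group) for 10% attrition. The same section calls one-way ANOVA a conservative planning device and assigns the primary analysis to covariate-adjusted longitudinal models.

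**The analysis.** The Abstract names repeated-measures ANOVA. Clinical data analysis names one-way ANOVA or Kruskal-Wallis, repeated-measures ANOVA, and a covariate-adjusted regression for MoCA change. It promises effect sizes and 95% confidence intervals for between-group differences in MoCA change. None of these places names a primary contrast.

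**The shared treatment.** Research design gives L-DLPFC rTMS to all three groups. The Discussion grants that "it is important to acknowledge that this approach may reduce the significance of intergroup differences", then says that sample size estimation, together with the enrolment criteria, secured enough power.

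**The concern.** An omnibus test of three means can be significant for reasons unrelated to the hypothesis. If acupuncture helps and magnetic stimulation does nothing, the test can still be positive. With no contrast named, the stated 80% does not tell the reader how likely the trial is to detect a MAG effect. The choice of which pairwise difference carries the conclusion also stays open until the data are seen.

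The planning effect raises a second difficulty. It is drawn from rTMS studies, whereas here rTMS is common to every arm and the randomised difference is a PC6 add-on. The Discussion recognises that this may shrink the differences and says the calculation meets the problem, but the Sample size section shows no step that does so.

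**Working it through.** **Inputs (Sample size section).** k = 3 groups, f = 0.32, alpha = 0.05, N = 99, 33 per arm. Below, d is the MAG minus SHM difference in within-group SD units.

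**1. The plan's own figure.** Noncentral F with df 2 and N − 3, noncentrality N × f² = 99 × 0.32² = 10.14. Power is 0.808. The smallest N reaching 0.80 is 98, or 99 with equal groups. The stated 99 is reproduced.

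**2. What f = 0.32 implies for MAG versus SHM.** f is the SD of the three group means divided by the within-group SD.
- Three equally spaced means: the extremes differ by f × √6 = 0.32 × 2.449 = 0.784.
- Two equal means and one different: the gap is f × √4.5 = 0.32 × 2.121 = 0.679.
- ACU best, MAG halfway between ACU and SHM: 0.784 / 2 = 0.392.
- Only ACU differs: d = 0.

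**3. Power for MAG versus SHM.** Two-sample noncentral t, df = 64, noncentrality d × √(33/2) = d × 4.062, two-sided 0.05. Omnibus power depends only on f, so it is the same in every row.

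| Position of ACU | d | Noncentrality | MAG–SHM power | Omnibus power |
|---|---|---|---|---|
| Midway between MAG and SHM | 0.784 | 3.18 | 0.88 | 0.81 |
| Equal to MAG or equal to SHM | 0.679 | 2.76 | 0.78 | 0.81 |
| Best arm, MAG midway | 0.392 | 1.59 | 0.35 | 0.81 |
| Only ACU differs | 0 | 0 | 0.05 | 0.81 |

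In the last row the 0.05 is the false-positive rate. A simulation of 40,000 trials gave the same 0.808 for the omnibus test when only ACU differs.

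**4. Detectable MAG–SHM difference.** With 33 per arm, 80% power is reached at d = 0.70. Loss of 10% from 35 leaves 35 × 0.9 = 31.5 per arm; at 31 per arm the figure is d = 0.72.

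**5. If the add-on effect is smaller than planned.** The documents give no figure for this, so these values are assumptions.
- Omnibus power at N = 99: 0.58 for f = 0.25 and 0.40 for f = 0.20.
- MAG–SHM power at 33 per arm: 0.67 for d = 0.6, 0.52 for d = 0.5 and 0.36 for d = 0.4.

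**6. The Discussion against the Sample size section.** The Discussion says sample size estimation answers the dilution from shared rTMS. The Sample size section gives the source of f, its value, the software and the attrition step. It shows no reduction of f and no argument that 0.32 suits an add-on.

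**The case against.** **One-way ANOVA is the planning model, not the primary test.** This stands. A reader might infer that the trial will be judged on the omnibus F; the Sample size section instead assigns the primary analysis to covariate-adjusted longitudinal models. The replacement names no contrast either, so the gap remains.

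**Confidence intervals are promised.** Between-group differences in MoCA change would show a null MAG–SHM effect if only ACU differed. This limits the harm to interpretation. It does not say which difference decides the trial.

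**The power loss may be nil.** If MAG and SHM are the extreme arms and f holds, power of 0.78 to 0.88 brackets the stated 0.80. This also stands: the documents do not show that the trial is underpowered for MAG versus SHM, only that the 80% does not refer to it.

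**Type I error.** A reader might infer that three MoCA comparisons inflate the familywise error, since multiplicity control is described only for imaging. The document does not plan three ungated pairwise tests. If pairwise tests followed a significant omnibus test, three groups would hold the error at about 5% (5.1% in simulation). Such a gate is not stated either; it would put MAG–SHM power at 0.73 to 0.80 when those arms are the extremes.

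**The origin of f.** A reader might infer that 0.32 is an rTMS-versus-sham effect and therefore too large. The cited studies are not at hand, and the text does not say what they compared or whether their effects were already reduced. Only the missing justification can be held against the plan.

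**The objective covers three arms, and contrasts can be left to an analysis plan.** Both are fair. But the hypothesis is directional for MAG, and the power claim and the claim of compensation are made in this article.

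**Conclusion.** The point holds and should be fixed. The 99 is correct for a three-group omnibus test, but its 80% is not power for the stated hypothesis. At the same f = 0.32, MAG–SHM power runs from 0.88 down to 0.05 according to where ACU falls, and no analysis designates that contrast as primary. The Discussion's statement that the calculation makes up for shared rTMS has no support in the Sample size section.

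These figures assume equal arms, a common SD and no covariate adjustment. Adjustment may raise precision, but it does not change which question the 80% answers. How far f = 0.32 overstates a PC6 add-on effect, if at all, cannot be determined from the document; the smaller f and d values are illustrations.

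**What to change.** Before unblinding:

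1. Name MAG minus SHM in MoCA change from baseline to week 3 as the single primary contrast, two-sided 0.05, from the covariate-adjusted model. Test MAG minus ACU after it, and label other comparisons secondary.
2. Restate power for that contrast: 80% for d = 0.70 with 33 per arm, and for about d = 0.72 with 31 per arm after attrition.
3. Either justify f = 0.32 for a PC6 add-on to rTMS, or delete the Discussion's claim that the calculation compensates for the shared treatment.

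The cost is wording in the Sample size, Clinical data analysis and Discussion sections, with no additional patients. The price is that MAG versus ACU moves to second place and the power statement becomes less favourable.

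### The recruitment target of 105 allows for 5.7% attrition, not the stated 10%; 99 evaluable patients at 10% loss need 110, or 111 with equal arms

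*Protocol article*

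**What the plan says.** All the relevant figures stand in the Sample size section of the protocol article.

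- Design and endpoint: "three-arm, parallel-group, randomized controlled design (1:1:1 allocation), with the MoCA score as the primary endpoint".
- Planning test: "One-way analysis of variance (ANOVA) is used to compare differences among the three groups".
- Effect size: "we adopt Cohen’s f ≈ 0.32 as the expected effect size".
- Result of the G*Power step at alpha 0.05 and power 0.80: "the estimated total sample size is 99 (33 per group) to detect significant differences in MoCA scores".
- Inflation for loss: "To account for a potential 10% attrition rate, the final recruitment target is set at 105 participants (35 per group".

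The Methods part of the Abstract repeats 105 patients, 35 per arm. The Sample size section adds that the one-way ANOVA was a conservative choice, because the within-subject correlation and covariate R² were not known, and that the covariate-adjusted longitudinal analysis should be at least as efficient. The Discussion later answers a worry about small between-group differences with the assurance that "we ensured sufficient statistical power through rigorous sample size estimation and balanced enrollment criteria".

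**The concern.** The section gives an evaluable number, an attrition rate and a recruitment target. Any two of these fix the third, and the third does not match what is printed. A reader will take it that the trial can lose one patient in ten and still have the 99 that its power statement requires. It cannot.

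What is at stake is the truth of a stated design property: 80% power after 10% attrition. The Discussion relies on the sample size estimate when it concedes that giving active rTMS to every arm may shrink the group differences. The base calculation also has little slack, since 99 patients give 0.808 against a target of 0.80.

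**Working it through.** **Inputs, all from the Sample size section:** three groups, 1:1:1; one-way ANOVA omnibus F test; f = 0.32; alpha 0.05; power 0.80; 99 evaluable; 10% attrition; 105 recruited. (The two-tailed label has no bearing on an omnibus F test.)

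**Step 1. Reproduce the 99.** Power = P(F′ > F_crit), where F′ is noncentral F with 2 and N − 3 degrees of freedom and noncentrality λ = N × f².

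- At N = 99, λ = 99 × 0.32² = 10.14 and F_crit(0.95; 2, 96) = 3.091, so power = 0.808.
- N = 97 gives 0.799 and N = 98 gives 0.804. The smallest sufficient N is 98, which becomes 99 with equal arms.

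The plan's figure of 99 reproduces exactly.

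**Step 2. Inflate for 10% loss.**

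| Method | Enrolled |
|---|---|
| 99 / (1 − 0.10) | 110 |
| Per arm, 33 / 0.90 = 36.7, rounded up to 37, × 3 | 111 |
| Shortcut 99 × 1.10 = 108.9 | 109 |
| From the unrounded minimum, 98 / 0.90 = 108.9 | 109 |
| From the unrounded minimum, 98 × 1.10 = 107.8 | 108 |
| Stated in the plan | 105 |

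None of these conventions gives 105.

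**Step 3. What 105 does allow.** 1 − 99/105 = 6/105 = 5.7%. At the stated 10%, 105 × 0.90 = 94.5 patients remain (31.5 per arm).

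**Step 4. Power on the plan's own test, f = 0.32.**

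| Evaluable N | Power | Detectable f at 80% power |
|---|---|---|
| 105 (no loss) | 0.833 | 0.307 |
| 99 | 0.808 | 0.317 |
| 95 | 0.790 | – |
| 94 | 0.786 | 0.325 |
| 93 (31 per arm) | 0.781 | 0.327 |

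The shortfall is 110 − 105 = 5 patients, or 111 − 105 = 6 with equal arms. It costs 1.4 to 1.9 points of power against the stated 0.80, or 2.2 to 2.7 points against the 0.808 that 99 patients would give.

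**The case against.** The best reply accepts the arithmetic and disputes its importance.

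- **The shift is smaller than the uncertainty in the input.** The effect size was adopted because no clear expected value was available. A change in detectable f of about 0.01 will not alter how the trial is read. This stands, and it limits the weight of the point. It does not make the sentence correct.
- **The primary analysis will be adjusted for covariates.** On the planning f = 0.32, defined on the unadjusted standard deviation, and charging six degrees of freedom for covariates, an R² of about 0.036 at N = 94 or 0.046 at N = 93 would bring power back to 0.80. That is a low bar. However, the section says R² was unavailable, puts no figure on the gain and does not set it against attrition. The stated 0.80 is the power of the unadjusted test. What stands is that the loss of power should be described as belonging to that planning model.
- **The ITT analysis keeps everyone.** The Clinical data analysis section says: "In the ITT analysis, missing outcome data will be handled using multiple imputation under the assumption of missing at random". Imputation does keep all randomised patients in the analysis, and a patient who misses week 3 but attends at week 8 or 12 may contribute some information. Imputing an outcome does not in general restore the information lost with it, though. A per-protocol analysis is planned as well, and imputation does not protect that.
- **The Discussion sentence is about diluted group differences, not attrition.** This is true. It still rests its assurance on this sample size estimate, so the correction bears on it, though only slightly.

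**Conclusion.** The statement is wrong as written. With 99 evaluable patients required, 105 recruited allows for 5.7% attrition; a 10% allowance needs 110, or 111 in equal arms. The error is confined to the inflation step, because the 99 is right.

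The effect is small: power of about 0.79 (0.781 to 0.786) instead of at least 0.80 if 10% are lost. That power figure assumes f = 0.32, alpha 0.05, an unadjusted one-way ANOVA, loss spread evenly over the arms, and no information recovered by imputation or covariate adjustment. The 5.7% and the 110 to 111 need none of these assumptions; they follow from the plan's own 99, 105 and 10%. The sentence should be corrected, but the design is not undermined.

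**What to change.** Keep 105 and replace the attrition sentence in the Sample size section with one to this effect: *The recruitment target of 105 (35 per group) allows for 5.7% attrition. If 10% are lost, about 94 patients are evaluable and the power of the unadjusted one-way ANOVA used for planning is about 0.79 at f = 0.32.* Remove the claim that 105 absorbs a 10% loss. The power assurance in the Discussion should then be read, or lightly reworded, in line with this.

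This costs one sentence and a slightly less favourable stated figure. It needs no extra patients and changes neither design nor analysis.

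If the sponsor prefers to keep both 80% power and the 10% allowance, the target becomes 110, or 111 (37 per group) under 1:1:1 allocation. That means 5 to 6 more patients and a matching change to the Abstract. With 111 enrolled, 10% loss leaves 99.9, which restores power of about 0.81.
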